## Methods

### Study Design and Setting

This population-based study adopts a test-negative case-control design to analyze COVID-19 VE against symptomatic and fatal SARS-CoV-2 infection from available health care datasets in the Special Capital Region of Jakarta, one of the provinces with the highest population density (15,900 people per km^2^ in 2020) and case rate per population relative to other regions in Indonesia [9]. Despite its robust development and economic growth, the contrast between rich and poor neighborhoods was highly prevalent in many parts of Jakarta’s districts [8,10].

This study will estimate VE against COVID-19 during the period of interest, which were the COVID-19 waves associated with the Delta and Omicron variants, from June 1 to August 31, 2021, and January 1 to April 2, 2022, respectively. Within each of these periods, a cycle of sustained upward and downward trends of the test positivity rate was observed [11-15] (Figure 1). Furthermore, the Delta and Omicron variants were estimated to be responsible for around 90% of SARS-CoV-2 infections in Jakarta during these two periods [14,16].

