### Study Variables

The primary outcome in this study is symptomatic SARS-CoV-2 infection, defined as a positive RT-PCR test within 10 days from the onset of influenza-like illness. The secondary outcome in this study is fatal SARS-CoV-2 infection, defined as death within 30 days after a positive RT-PCR test result [24]. Meanwhile, the primary exposure in this study was vaccination status, which can be classified as unvaccinated, dose 1 or partial vaccination, dose 2 or primary vaccination, and booster dose. People without any vaccination entries after data linkage with the PCARE Vaksin dataset at the end of each period of interest will be classified as unvaccinated persons. For vaccinated people, we will only consider the last vaccination data entry that happened before the patients’ index RT-PCR test date.

Several covariates should be assessed as potential confounders in the study, such as age in years at the index test date, gender, calendar week of the RT-PCR collection during the period of interest, living in impoverished neighborhoods, presence of any comorbidities, occupation, and reinfection status. The calendar week of the RT-PCR collection during the period of interest will be presented as a whole number starting from week 1 as the start of the period of interest. Living in an impoverished neighborhood will be presented as a dichotomous variable. People will be classified as living in an impoverished neighborhood if their neighborhood number at the subdistrict level is listed as one of the impoverished neighborhoods in the 2018 Jakarta Governor’s regulation concerning improving the quality of settlements in residential areas. Occupation will be presented as categorical variables that consist of health care worker, public or government official, and civilian. Reinfection or people with previous SARS-CoV-2 infections will be presented as a dichotomous variable. People with a previous positive RT-PCR SARS-CoV-2 result that occurred more than 90 days after the current case will be classified as people with a previous SARS-CoV-2 infection [25].

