To control for unmeasured confounders [26], such as societal preventive measures or the changing dynamic of the viral transmission within the community, this study will match each case with a control using a ratio of 1:2 by matching for age within 10 years of the case’s age, gender, and the calendar week of the RT-PCR collection during the period of interest. The matching procedure will be assessed with standardized mean differences, with values less than 0.1 indicating sufficient matching [27,28].

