### Data Sources

This study will analyze the final datasets derived from the integration of several datasets provided by the Jakarta Provincial Health Office, Ministry of Health, and Social Security Agency on Health after April 2022 (Table 1). Variables such as ID number and date of birth will be used for the dataset linkage (Figure 2). From the New All Records (NAR) and Suspect and Probable (SUSPROB) datasets, symptomatic people with a positive or negative first RT-PCR test result within each of the periods of interest will be identified as cases or controls. Furthermore, people identified as cases will be linked to the entries in the REV POS dataset to extract the outcome of their disease course (Figure 2). People with incomplete data for ID number, date of birth, gender, swab collection date, PCR test result, domicile address, outcome, and date of death (if the case ends in death) will be excluded from further data linkage.

**Table 1 table1:** List source for merged datasets.

Name	Developer	Description	Variable identified
NAR^a^	Ministry of Health Republic of Indonesia	Record of all RT-PCR^b^ SARS-CoV-2 tests carried out by affiliated laboratories	Name ID number Date of birth Sex (male, female) Comorbidity Domicile address Laboratory name Reason for testing Swab collection date RT-PCR result confirmation date RT-PCR testing result
SUSPROB^c^	Jakarta Provincial Health Office	Record and follow-ups of all people with influenza-like illness or probable COVID-19	Name ID number Date of birth Sex (male, female) Comorbidity Domicile address Presence of influenza-like illness (fever, chill, cough, etc) Date of symptom onset Travel history Plan swab testing date Swab collection date RT-PCR testing result
REV POS	Jakarta Provincial Health Office	Records and follow-ups on all positive cases in Jakarta	Name ID number Date of birth Sex (male, female) Comorbidity Domicile address Date of swab collection Case severity (asymptomatic, mild, moderate, severe) Outcome (survived or death) Date of death
PCARE^d^ Vaksin	Social Security Agency on Health Indonesia (BPJS Kesehatan)	Record of all administered COVID-19 vaccines and their recipients	Name ID number Date of birth Sex (male, female) Domicile address Occupation or vaccination batch group (health workers, government officials, elderly, children, civilians) Name of health care facility/vaccination center Vaccination date Vaccination ticket number Vaccination dose Vaccine name Vaccine batch/lot number

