One main logistic model will be assembled by forward inclusion, and only covariates with less than 20% missing data will be considered to be included in the model building. Assessment for confounders and effect modifiers will be performed with the Wald test and by observing the change in the primary exposure coefficient SE. Covariates that act as confounders will be included in the model. If effect modification is present, it is essential to report VE and CIs for each subgroup individually. The linearity between continuous variables and the log odds of having symptomatic SARS-CoV-2 infection will be assessed, and the continuous variables will be modified into categorical variables if necessary. The overall fit of the final multivariate logistic regression model will be assessed with Hosmer and Lemeshow goodness-of-fit test [30], as matching might incur matching-related bias from the cases and controls having similar exposure, thus underestimating the aVE. We will also perform conditional logistic regression as a sensitivity analysis for measuring the aVE estimation against symptomatic SARS-CoV-2 infection or our primary objectives [31,32]. Furthermore, for the analysis of the Omicron period, we will perform an additional analysis of relative VE (rVE) by comparing recipients of one booster dose to recipients of the 2 doses who were eligible to receive the booster dose. The rVE will be calculated using the formula rVE = [(aVE from booster dose – aVE from 2 doses and eligible for booster)/(1 – aVE from 2 doses and eligible for booster)] × 100%. For the rVE analyses, we will include only people whose last booster dose was within 7 to 90 days before their index test date and compare them to people whose last 2-dose vaccination date was ≥90 days before their index test date [24].

This study will also conduct subgroup analyses based on the time between the last vaccination date and test index date to assess for waning of immunity (Table 2). These subgroup analyses will be conducted separately for each wave and vaccine brands or regimens. Similar to the main analysis, each vaccinated subgroup will be compared to unvaccinated people.

**Table 2 table2:** Subgroup analysis based on time since last vaccination.

Subgroup	Description
1	7-14 days between the last vaccination dose and index test date
2	14-28 days between the last vaccination dose and index test date
3	28-56 days between the last vaccination dose and index test date

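### Calendar-week matching cannot control differences between areas in the same week, and the only place-derived covariate named is an optional binary deprivation flag although every retained record carries an address

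*Protocol article*

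**What the plan says.** Under Study Variables, the protocol article gives the reason for matching as "To control for unmeasured confounders [26], such as societal preventive measures or the changing dynamic of the viral transmission within the community". The factors are fixed: "matching for age within 10 years of the case’s age, gender, and the calendar week of the RT-PCR collection during the period of interest".

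The named candidate covariates are age, gender, and then "calendar week of the RT-PCR collection during the period of interest, living in impoverished neighborhoods, presence of any comorbidities, occupation, and reinfection status". One of these derives from place: "Living in an impoverished neighborhood will be presented as a dichotomous variable". A person is flagged "if their neighborhood number at the subdistrict level is listed as one of the impoverished neighborhoods in the 2018 Jakarta Governor’s regulation". Statistical Analysis sets how covariates enter: "One main logistic model will be assembled by forward inclusion, and only covariates with less than 20% missing data will be considered".

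Under Data Sources, Table 1 lists domicile address in NAR, SUSPROB, REV POS and PCARE Vaksin, and records with incomplete address are dropped before further linkage. Laboratory name is listed for NAR only, the dataset described as "Record of all RT-PCR^b^ SARS-CoV-2 tests carried out by affiliated laboratories". The setting section says that "the contrast between rich and poor neighborhoods was highly prevalent in many parts of" Jakarta's districts.

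**The concern.** Two people of similar age and the same gender, tested in the same week, can live in areas with different transmission and different vaccine uptake. Matching on week does not separate them. If both factors vary by area, area confounds the odds ratio from which VE is calculated.

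The article makes this path plausible. Its Introduction says that social and economic characteristics affect both vaccine acceptance and disease outcomes, and describes Jakarta as socioeconomically segregated. Its Table 3 of potential biases has no row for area.

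The neighborhood flag is a partial control. It records deprivation as listed in 2018, does not change over the epidemic, and treats all listed neighborhoods as one group and all others as another. It may also fail to enter the model. The planned conditional logistic regression uses the same matching factors and would not show the gap.

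The brand- and dose-specific VE estimates are at stake. A bias of this kind does not shrink with the expected 400,000-900,000 people.

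**Working it through.** **The plan's own precision figure.** Sample Size gives about 5000 cases and 10,000 controls per analysis, for coverage 20%-90%, VE 50%-90%, precision ±5% and type 1 error 0.05. Take OR = 1 − VE, coverage in controls p0, and p1 = OR·p0/(1 − p0 + OR·p0). Then cases = z²[1/(p1q1) + 1/(2·p0q0)]/D², with D = 0.05/OR.

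The most demanding corner is VE 50% with coverage 20%:
- p1 = 0.1/0.9 = 0.111, so 1/(p1q1) = 10.125.
- 1/(2 × 0.16) = 3.125.
- Cases = 3.8415 × 13.25/0.01 = 5090. With D = asinh(0.05/OR) the result is 5107.

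At 1:2 the total is about 15,300. The stated figure reproduces within 3%, with ±5% read as ±5 VE points. That gives a yardstick for the bias.

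**Bias from omitting area.** The article gives no coverage or incidence by area, so these inputs are assumptions. Take two areas with equal numbers of controls, the same age, gender and week mix, and the same true OR. Coverage in controls is c1 and c2. The case-to-control ratio among unvaccinated people in area 1 is r times that in area 2. Collapsed over area:

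OR without area = (1 − VE) × [(c1·r + c2)/((1 − c1)·r + (1 − c2))] ÷ [(c1 + c2)/(2 − c1 − c2)]

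Example with VE 50%, c1 = 0.4, c2 = 0.6, r = 2:
- Vaccinated cases: 0.5 × (0.8 + 0.6) = 0.7.
- Unvaccinated cases: 1.2 + 0.4 = 1.6.
- The vaccination odds in controls are 1, so OR = 0.7/1.6 = 0.4375 and VE = 56.25%.
- With the higher ratio in the high-coverage area instead, OR = 0.8/1.4 = 0.571 and VE = 42.9%.

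| True VE | Coverage by area | Ratio | VE, more transmission where coverage is low | VE, more transmission where coverage is high |
|---|---|---|---|---|
| 50% | 45% / 55% | 1.5 | 52.0% | 48.0% |
| 50% | 45% / 55% | 2 | 53.2% | 46.6% |
| 50% | 40% / 60% | 1.5 | 53.8% | 45.8% |
| 50% | 40% / 60% | 2 | 56.25% | 42.9% |
| 70% | 40% / 60% | 2 | 73.8% | 65.7% |
| 90% | 40% / 60% | 2 | 91.3% | 88.6% |

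If c1 = c2, or if r = 1, the bracketed terms cancel and the shift is zero. Stratifying or adjusting by area returns the true VE in every row. Area multiplies the OR by a factor that does not depend on VE, so the shift in points at VE 90% is one fifth of that at 50% (0.1/0.5). Among the rows at VE 50%, only the 20-point gap with a 2-fold ratio goes beyond ±5 points.

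**The case against.** The strongest reply is that the matching sentence is about time. It speaks of a changing dynamic, and Table 3 says week matching addresses exposure risk over the periods of interest. Calendar-week matching is an ordinary tool for that. This largely stands: the article does not claim in so many words to control local transmission. The wording, with preventive measures named beside transmission, is still broader than what age, gender and week can deliver.

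Second, a reader might infer that no place factor is used at all. That is not so. The neighborhood flag derives from place and targets the rich-poor contrast that the article describes.

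Third, the covariate list opens with wording that marks it as examples, and details of the final and matched datasets are referred to appendix tables that are not at hand. District could be among the variables there. This weakens any claim that area was overlooked. It does not change the matching factors, which are explicit, and any further covariate would face the same forward-inclusion rule. The article does say that covariates found to act as confounders will be included, but it leaves that to selection.

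Fourth, the causal premises are incomplete. Rollout is described by brand, date and health care worker priority rather than by area, and occupation is already a candidate covariate. Nothing shows that test access differs by laboratory. This stands, and it is why the confounding is called possible.

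**Conclusion.** The point holds in a limited form. Matching on age, gender and week controls city-wide time and leaves differences between areas within a week to an optional binary flag, while a finer geographic variable can be derived from data already held. The result is possible area confounding of VE, of unknown size and direction. Under the assumed gaps of 10 to 20 points and ratios of 1.5 to 2, the shift is about 2 to 7 points at true VE 50%. For the 20-point gap with a 2-fold ratio it is about 1 point at 90%. It is zero if either factor is even across areas. These figures ignore whatever part of the difference the neighborhood flag would remove.

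A reader might go further and infer that the estimates are confounded, or that the error is near 10 points. Coverage of 70% against 40% with a twofold ratio does give 59.1% or 38.6% at true VE 50%. But that requires a 30-point gap between areas within the same week, and the article reports no area-level coverage or positivity to support it.

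**What to change.** Include municipality or district of domicile as a fixed main effect in the absolute and relative VE models, outside the forward selection. Keep the 1:2 matching as it is, so that no cases are lost.

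Run two sensitivity analyses only:
- A district-by-period interaction, where cells allow. Models are split by wave, brand or platform, and dose, and again by six time-since-vaccination bands, so forcing the interaction everywhere would be hard to defend.
- Testing laboratory, where NAR records it. Laboratory is not listed for SUSPROB and may partly reflect how a person sought testing, so it should not be in the main model.

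Reword the matching sentence to say that matching controls age, gender and city-wide calendar time, and that area is handled in the model.

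The cost is modest. Assigning the neighborhood flag already requires residence to be coded at subdistrict level, so district should follow with little extra work. The downside is a small loss of precision in the smaller brand-and-dose analyses. The main effect removes average differences between districts over a wave. It does not remove differences within districts, and those that change from week to week are examined only in the interaction analysis. The article describes the analysis as still underway, so at that stage the change was feasible.

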### Study Participants

The study will include people 18 years or older who domiciled in Jakarta and underwent an RT-PCR test for SARS-CoV-2 infection due to symptoms of influenza-like illnesses within 10 days of the test date. Although people may have more than one RT-PCR result during the period of interest, this study will only account for the first positive or negative result per person as the index test date for each of the COVID-19 waves. People who had at least one sample with a positive SARS-CoV-2 RT-PCR result during the period of interest will be classified as cases, while people with a negative SARS-CoV-2 RT-PCR without any positive results over the period of interest will be classified as controls.

People with a positive RT-PCR test result within 90 days of the preceding index test date, with inconclusive RT-PCR results, who received different vaccines for dose 1 and dose 2 or a heterologous primary vaccine series, or who had a time interval between dose 1 and dose 2 that was less than the government recommendation (<21 days for Pfizer and Sinopharm, <28 days for CoronaVac and Moderna, and <12 weeks AstraZeneca) will be excluded from the analysis. We will also exclude people with incomplete vaccination records, such as people who declared receiving 2 vaccine doses without being able to verify the previous dose.

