### Sample Size

The calculation formula for the sample size used in this study will follow the methodology described by O’Neill [29]. Assuming vaccination coverage between 20%-90%, a precision of ±5%, a type 1 error rate of 0.05, and an anticipated VE of 50%-90%, the minimum sample size needed for each specific COVID-19 vaccine brand and dose VE analysis is roughly around 15,000, with 5000 cases and 10,000 controls [24,29] (Table S4 in Multimedia Appendix 1).

We expect to analyze 400,000-900,000 people after the aggregation of all datasets. Therefore, we should have enough data to conduct the VE analyses for each specific COVID-19 brand and regimen in our final dataset. We will compare the proportion of COVID-19 vaccines received by eligible people in our dataset during each period of interest to those reported by the Ministry of Health [17] (Table S1 in Multimedia Appendix 1). Furthermore, we will exclude people who received COVID-19 vaccine brands with vaccination coverage of less than 20%, as these vaccines are usually distributed briefly in the population or only available to specific subgroups within the community. Moreover, we might consider combining different COVID-19 vaccine brands with the same platform into one group to decrease the required sample size, especially for the subgroup VE analysis [24].

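### A ±10-year age match accepted on one overall SMD below 0.1 can leave age gaps of about 4 years, in opposite directions, at the two ends of the age range

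*Protocol article*

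**What the plan says.** Under Study Variables, the protocol article will "match each case with a control using a ratio of 1:2", "by matching for age within 10 years of the case", together with gender and calendar week of sampling. The only adequacy test is given next: "The matching procedure will be assessed with standardized mean differences, with values less than 0.1 indicating sufficient matching". No check by age band is stated, and nothing is said about which control is taken when several fall inside the caliper. The lower age limit is set under Study Participants: "The study will include people 18 years or older".

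Age also has a possible place in the model: "Several covariates should be assessed as potential confounders in the study, such as age in years at the index test date". The Statistical Analysis section takes VE from an adjusted odds ratio in an unconditional logistic model built by forward inclusion. Confounders are judged by the Wald test and by the change in the standard error of the exposure coefficient. Continuous variables are checked for linearity against the log odds of infection and categorised if necessary. For the primary objective it adds: "We will also perform conditional logistic regression as a sensitivity analysis".

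**The concern.** A caliper of 10 years either way is a window of about 20 years. If controls are drawn from it at random, most come from the side where tested people are more numerous. With fewer tested people at older ages, older cases get younger controls. At the lower limit of 18 the window is cut off below, so the youngest cases get older controls. A single mean difference over all ages adds these opposite errors together and can look small when the match is poor at both ends.

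This matters for VE only if uptake differs by age inside the window. Table 1 lists the elderly as a vaccination batch group of their own, so a steep change is plausible. The conditional analysis relies on the matched sets for control of age. The Statistical Analysis section already expects matching to bias VE downward. Residual age confounding of the kind shown below also lowers VE, so a gap between the two models could be put down to the wrong cause.

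**Working it through.** **The plan's own figure.** The Sample Size section gives about 5000 cases and 10,000 controls per brand-and-dose analysis. The precision formula for VE = 1 − OR with two controls per case is n(cases) = 1.96² × (1 − VE)² × [1/(p1q1) + 1/(2·p0q0)] / 0.05². At VE 50% and coverage 20%, p0 = 0.20, the case odds are 0.5 × 0.25 = 0.125 and p1 = 0.111. The bracket is 10.125 + 3.125 = 13.25, so n ≈ 3.84 × 0.25 × 13.25 / 0.0025 ≈ 5090 cases, or 15,270 people in all. The figure is reproduced. The point does not depend on it, but it supplies the scale used below.

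**Inputs from the article:** caliper ±10 years, ratio 1:2, lower age 18, threshold 0.1.

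**Inputs assumed, because the article does not give them:** ages 18-90, roughly normal; test-negatives centred at 38 and cases at 38-42, SD 14-15; controls drawn at random within the caliper; true VE 50%; coverage stepping at age 60, either 80% against 30% or 70% against 40%.

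**Step 1: balance.** For a case aged a, the control age density is proportional to f0 within a ± 10. Averaging over case ages gives:
- overall age SMD 0.01-0.05, which passes;
- controls 3.6-4.0 years younger for cases aged 60-69, and 4.9-5.3 years younger for cases aged 70 and over;
- 37-45% of the controls of cases aged 60 and over are under 60.

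An SMD of 0.1 at SD 14-15 is 1.4-1.5 years, while a 4-year gap is 4/15 = 0.27 to 4/14 = 0.29 of the same SD. A different assumption (age 18 plus a gamma variable, matching without replacement) gave the same pattern: controls 2.7-3.8 years younger for older cases, about 4 years older for cases under 25, overall SMD 0.01-0.09. With ±2 years the gaps were about 0.2 and 0.4 years. With nearest-age selection inside ±10 years they were 0.0 in every band.

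**Step 2: why this reaches VE.** Take cases aged 60 and over, the 80%/30% step, and 40% of their controls under 60. The controls' coverage is 0.60 × 0.80 + 0.40 × 0.30 = 0.60, odds 1.5. The case odds are 0.5 × 0.80/0.20 = 2.0. The odds ratio in that band is 2.0/1.5 = 1.33 instead of 0.50. Cases in their fifties err the other way, because some of their controls are 60 or over, so only part of this survives overall.

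**Step 3: overall VE (true value 50%).** Conditional estimates without age are roots of the 1:2 conditional-likelihood score. The other rows are simulated matched sets.

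| Uptake step at 60 | Analysis | ±10 years | ±2 years |
|---|---|---|---|
| 80%/30% | conditional, no age | 44.7-46.7% | 49.3-49.5% |
| 80%/30% | conditional, linear age | 46.0-47.2% | not tabulated |
| 80%/30% | age in bands | about 50% | not tabulated |
| 80%/30% | unconditional, no age | not tabulated | 45.5-46.9% |
| 70%/40% | conditional, no age | 47.8-48.7% | 49.8% |

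The shortfall in the conditional analysis without age is 50 − 46.7 = 3.3 to 50 − 44.7 = 5.3 points under the steeper step, and 50 − 48.7 = 1.3 to 50 − 47.8 = 2.2 points under the milder one.

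**Step 4: does the model rescue it?** Where uptake was instead assumed linear in age on the log-odds scale, adding age at ±10 years gave VE 48-51% in the unconditional model and 49% in the conditional one. Under a step, linear age was not enough in the conditional model, while age bands were. The tighter caliper alone did not repair an unconditional model lacking age.

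**The case against.** A reader might infer that age confounding stays in the reported VE. The documents do not support that. Age in years is the first confounder named, VE is an adjusted odds ratio, confounders are to enter the model, and continuous variables can be categorised. With 5000 cases and 10,000 controls the Wald z for age was about 4-11 where uptake was linear in age, so age would very probably be admitted. Nothing says that age is dropped from the conditional model, which is in any case a sensitivity analysis. Most of this stands.

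Three gaps remain. First, age is a candidate and is not forced in; under the assumed uptake steps the Wald z was 1.8-6.7, so entry is likely but not certain. The second criterion, a change in standard error, does not measure confounding. Second, the linearity check concerns age against infection, so it need not reveal a step in uptake. Third, linear age left a shortfall under such a step.

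A reader might also infer that older cases will systematically receive younger controls. That depends on random choice within the caliper and on fewer tested people at older ages. The article states neither, and with nearest-age selection the gap vanishes.

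It is also fair to say that a narrower caliper alone is neither sufficient nor strictly necessary, and that the milder shortfall lies inside the planned precision of ±5%. But a bias does not shrink as the sample grows, and the article expects far more than the minimum sample.

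**Conclusion.** The point holds as a weakness of the matching rule and its acceptance test. The stated criterion can pass a match that is about 4 years out, in opposite directions, at the two ends of the age range. This requires that controls are not chosen by nearest age.

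The consequence for VE is conditional. Residual age confounding can remain in the conditional sensitivity analysis, and in the unconditional model if age is omitted or entered only linearly while uptake changes steeply with age. The article gives no age distribution, no uptake by age and no selection rule, so the size cannot be set from it. The figure of about 1 to 5 VE points rests on the assumed ages, random selection, uptake steps at 60, a true VE of 50% and no age term in the conditional model. It does not show that the main VE estimate will be biased. This is a cheap improvement, not a fatal flaw.

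**What to change.** In Study Variables, match on a narrower age caliper, for example ±2 years, or take the nearest-age control within the present caliper, widening only where no control is found. State the selection rule. Require an age SMD below 0.1 within age bands (for example 18-29, 30-44, 45-59 and 60 and over) as well as overall.

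In Statistical Analysis, force age into both the unconditional and the conditional model as categories or a spline, instead of leaving it to forward inclusion. For the unconditional model this part matters most.

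The cost is one re-run of the match and a few lines of text. The article says "We expect to analyze 400,000-900,000 people after the aggregation of all datasets", which is encouraging, but that total mixes cases and controls. The control-to-case ratio by week, sex and age is not given, so some cases may still need the wider caliper; their number should be reported.
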